#### *Major adverse cardiovascular events (MACE)*

MACE as defined by cardiovascular death, hospitalisation for myocardial infarction, heart failure, or stroke, percutaneous coronary intervention or coronary artery bypass grafting [47], will be ascertained at the 6 and 12 month assessments. Attempts will be made to check GP records for all participants who do not complete the questionnaire and do not attend for follow-up at 12 months.

#### *Health related quality of life*

Health related quality of life data will be captured at recruitment, and at the 6 and 12 month assessments using EuroQoL 5D-3L (EQ-5D-5L) Index that has been used widely in COPD [48]. EQ-5D-5L was developed as a utility questionnaire and addresses mobility, self-care, usual activities, pain/discomfort and anxiety/depression. The completed instrument can be translated into quality of life utilities suitable for calculation of QALYs through the published UK tariffs.

#### *Disease related health status*

Disease related health status will be ascertained at recruitment and at the 6 and 12 month assessments by questionnaire using the COPD Assessment Test (CAT) [49-51]. The CAT is an 8-item unidimensional measure of health status impairment in COPD. The score ranges from 0-40; it correlates very closely with health status measured using the St George Respiratory Questionnaire and is reliable and responsive. The CAT score is preferred since it provides a more comprehensive assessment of the symptomatic impact of COPD.

The Baseline Dyspnoea Index (BDI) questionnaire will be included in the recruitment, assessment and the Transitional Dyspnoea Index (TDI) will be administered at the 6 and 12 month assessments [52]. The research nurse will ask open ended questions about breathlessness, the nurse will then interpret the responses and will select a score. BDI and TDI were developed in order to obtain a comprehensive understanding of patients' severity of breathlessness and are based on three components: functional impairment; magnitude of task; and magnitude of effort [52]. BDI is a discriminative instrument used to quantify the severity of dyspnoea at an initial or baseline state, whereas TDI is an evaluative instrument used to quantify the changes in dyspnoea from the initial or baseline state. [53].

In selected centres, the HARQ will be used to assess symptoms not elucidated by the CAT or dyspnoea index. This is a validated self-administered questionnaire which is responsive to treatment effects [54].

#### *Post bronchodilator lung function*

During the COVID-19 pandemic, lung function (an aerosol generating procedure) will not be assessed.

Outwith pandemics, lung function will be measured at recruitment, titration visits, and 6 and 12 months using spirometry performed to ATS/ERS standards [55]. Spirometry is a routine part of the clinical assessment of people with COPD. Post bronchodilator (LABA within 8 hours, short acting  $\beta_2$  agonist within 2 hours) FEV1 and FVC will be measured. If necessary, lung function will be measured 15 minutes after administration of the participant's own SABA. Widely used European Coal and Steel Community predictive equations will be used to

compute predicted values for FEV1, FVC [56]. As described in section 6.1, if spirometry is contraindicated, it should not be carried out.

#### *Health care utilisation*

Health care utilisation during the previous 6 months will be ascertained at recruitment and the 6 and 12 month assessments (see section 10.5).

#### *Adverse reactions and serious adverse events*

Adverse reactions and serious adverse events whilst on study medication will be ascertained at the 1, 2, 3 and 4 week titration assessments and the 6 and 12 month assessments. Serious adverse events/drug reactions will be subject to the serious adverse events reporting protocol (see section 9 for further details).

#### *Compliance*

Compliance with study medication will be assessed at the 1, 2, 3 and 4 week titration assessments and the 6 and 12 month assessments. Participants will also be asked to estimate their compliance at each visit. Outwith pandemics participants will be asked to return empty drug bottles and compliance will be calculated by pill counting, however during pandemics this will not be possible. Instead, participants will be asked to return any unused study medication to their local pharmacy and ask them to safely dispose of the medication. In these circumstances, no pill count will be possible.

#### *Mortality*

Deaths during the follow-up period will be reported as a SAE.

### **7.8 Long term follow-up assessments**

Participants will be contacted by telephone at an appropriate number of weeks after the end of the treatment period to confirm that they have successfully weaned off study medication, this will be recorded in the CRF.

- Participants on 4 tablets a day will be contacted after 4 weeks
- Participants on 3 tablets a day will be contacted after 3 weeks
- Participants on 2 tablets a day will be contacted after 2 weeks
- Participants on 1 tablet a day will be contacted after 1 week

### **7.9 Qualitative assessments**

Not applicable

### **7.10 Withdrawal criteria**

Participants may be withdrawn from treatment for any of the following reasons:

- Participant withdraws consent for treatment.
- Unacceptable adverse effects.
- Intercurrent illness preventing further treatment.
- Development of serious disease preventing further treatment or any change in the patient's condition that justifies the discontinuation of treatment in the clinician's opinion.
- Development or diagnosis of a condition for which beta-blockers are guideline recommended treatment e.g. myocardial infarction, heart failure with ejection fraction <40%, acute coronary syndrome.

If participants are withdrawn from treatment they will be asked whether they would be willing to remain in the trial and be followed up as per trial schedule or, failing this, to allow routine follow-up data to be used for trial purposes (hospital/GP medical records).

Participants who withdraw consent for study treatment will be advised to wean down the study medication as described in section 8.7.2. Participants withdrawn from treatment for other clinical reasons (i.e. side effects) will not be weaned, but advised to stop study treatment with immediate effect. Weaning of beta-blockers is advised when administered for cardiovascular indications, this is not the case in this trial.

Participants who wish to withdraw from study follow-up should be asked whether they would be willing to consent to allow routine follow-up data to be used for trial purposes (hospital/GP medical records).

Sites should encourage participants withdrawing from treatment to return all unused study medication to the local study centre for safe destruction of unused medication via Clinical Trials Pharmacy (in secondary care) or via Disposal of Unused Medication Boxes or Community Pharmacies (in primary care). If participants do not return unused medication to their local study centre, they should be encouraged to dispose of the medication safely, for example at their local Community Pharmacy. Their responsibilities in terms of safe return or disposal of study medication should be made clear to participants as part of the informed consent process.

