#### *General considerations:*

- As for heart failure, bisoprolol will be introduced in a 'start low, go slow' manner, with assessment of heart rate, blood pressure, FEV1 and clinical status after each titration. During the COVID-19 pandemic, FEV1 will not be assessed – rather the participants will be asked about any changes in their breathlessness occurring after starting/increasing study drug.
- Ideally dose titration will take place during the first seven weeks of the treatment period. However, as in everyday clinical practice, practical (e.g. time for participant to receive study treatment, participant availability, holidays) and clinical considerations (e.g. side effects, exacerbations) a degree of flexibility and clinical judgement is likely to be needed. The timing of dose titration visits must be 7 days or more apart. In most cases, the dose established by the end of week 7 after randomisation will be considered the dose for the remaining treatment period; but there will be some cases where this period is extended (for example due to frequent exacerbations during this period). The first study bottle containing 168 tablets provides sufficient for up to 14 days between each titration visit.
- Prior to commencing treatment participants will be advised:
  - not to expect immediate improvement and that any benefit is likely to be reflected in reduced exacerbations;
  - temporary symptomatic deterioration (fatigue, tiredness) may occur during the initiation/up titration phase but this can usually be easily managed by adjustment of bisoprolol therapy (usually to previous tolerated dose)
  - not to stop treatment without first consulting their research team.
- It will not be possible to reliably establish in an individual the treatment allocation from heart rate, blood pressure. In studies of bisoprolol in heart failure similar proportions of patients allocated to placebo and bisoprolol were unable to tolerate treatment [38].
- Once established on a treatment dose, no further titration assessments will be required.
- Once established on a specific treatment dose, it may be necessary to reduce dose either temporarily or for the remaining treatment period.
- Treatment should not be abruptly stopped (unless clinically indicated), but weaned off by one tablet a day per week to zero. Successful weaning will be confirmed by a telephone call from local research team.

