### **8.7.2 Dose reduction at end of follow-up**

Following completion of the 12 month dosing period participants will be weaned off study drug over the following weeks (3-2-1 tablet(s) od) in order to avoid possible rebound myocardial ischemia. A similar regime will be recommended for participants who wish to discontinue medication during the study.

| Maintenance dosage: | At final visit | Subsequent week |       |      |
|---------------------|----------------|-----------------|-------|------|
|                     |                | 1               | 2     | 3    |
| 1 tab               | Stop           |                 |       |      |
| 2 tab               | 1 tab          | stop            |       |      |
| 3 tab               | 2 tab          | 1 tab           | stop  |      |
| 4 tab               | 3 tab          | 2 tab           | 1 tab | stop |

Successful weaning will be confirmed by the research nurse by telephone one week after anticipated cessation of treatment. Successful weaning is defined as reduction of dose as described above prior to stopping. Any adverse effects experienced during weaning will be documented within the CRF.

Figure 3: Schematic representation of dose titration

[figure not shown]

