### *Medications known to significantly interact with bisoprolol*

- Calcium antagonists of the verapamil type and to a lesser extent of the diltiazem type: Negative influence on contractility and atrio-ventricular conduction.
- Ivabradine: Negative influence on atrio-ventricular conduction.
- Class I antiarrhythmic drugs (e.g. quinidine, disopyramide; lidocaine, phenytoin; flecainide, propafenone): Effect on atrio-ventricular conduction time may be potentiated and negative inotropic effect increased.
- Centrally acting antihypertensive drugs such as clonidine and others (e.g. methyl dopa, moxonidine, rilmenidine): Concomitant use of centrally acting antihypertensive drugs may worsen heart failure by a decrease in the central sympathetic tone (reduction of heart rate and cardiac output, vasodilation). Abrupt withdrawal of the antihypertensive drug, particularly if prior to beta-blocker discontinuation, may increase risk of "rebound hypertension".

These medications are listed in the eligibility criteria. Participants who are known to be taking one or more of these medications at baseline are not eligible for the study and should not be recruited.

If for clinical reasons a beta-blocker or a medication known to significantly interact with bisoprolol is deemed necessary then the study treatment will be discontinued and appropriate treatment instigated by the caring physician, no weaning will be required because of clinical necessity (although weaning can be carried out at the discretion of the treating clinician). Participants will be asked to remain in the study and be followed up in accordance with the trial protocol.

Despite these precautions, if participants are inadvertently prescribed a medication known to significantly interact with bisoprolol whilst taking BICS medication, this will be logged on a study log of interacting medication held by the trial office. If the participant experiences a serious adverse event (e.g. hospitalisation with complete heart block) as a result of the interaction, this will be recorded as (i) a serious adverse event within the study and assessments of relatedness and expectedness made and (ii) as a breach which would be assessed as serious or non-serious according to the definitions.

*Medications that may interact with bisoprolol and to be used with caution.* Participants on these medications at recruitment are eligible for the study, the dose titration will compensate for any interactions.

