## APPENDICIES

### Appendix 1 – Risk

Risks associated with trial interventions

- ☐ A ≡ Comparable to the risk of standard medical care  
☒ B ≡ Somewhat higher than the risk of standard medical care  
☐ C ≡ Markedly higher than the risk of standard medical care

Bisoprolol is licensed for the treatment of angina, hypertension and heart failure. In BICS bisoprolol will be used 'off label' to people with COPD. Heart failure guidelines state that for people with heart failure and COPD it is safe to use cardiac specific beta-blockers such as bisoprolol to treat heart failure as long as the initiating dose is low and there is a gradual dose titration. Systematic reviews demonstrate that cardiac specific beta blockers such as bisoprolol have no significant effect on lung function, symptoms or response to beta2 agonists when administered to people with COPD.

The main concern is that the administration of bisoprolol will induce bronchospasm (worsening of lung function). The risk of this has been minimised by excluding persons with a sole diagnosis of asthma, a diagnosis of asthma before the age of 40, moreover the dose of bisoprolol will be slowly titrated as recommended for heart failure and the maximum dose (5mg) is less than that recommended for heart failure.

It is anticipated that the side effect profile for bisoprolol will reflect that for use in people with heart disease. In heart disease it is recommended that any cessation of beta-blockers should be slow to prevent relapse/exacerbation of cardiac symptoms, in this trial the dose of bisoprolol will be slowly weaned to zero at the end of the treatment period. For participants with intolerable side effects, wherever possible the dose of bisoprolol will be weaned down to zero wherever possible, if not the study drug will be stopped immediately, this is deemed acceptable as these people have not been commenced on bisoprolol for cardiac disease.

The Chief Investigator, Clinical Trial pharmacist and Sponsor oversight committee have undertaken a review of the licensed vaccines and have confirmed that they would not expect any interaction between the COVID vaccines and the study IMP.

| What are the key risks related to therapeutic interventions you plan to monitor in this trial? |                                      | How will these risks be minimised?   |                                    |          |

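### Section 7.10 and Appendix 1 give opposite default instructions for participants who stop study drug because of side effects

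*Protocol*

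**What the plan says.** Five places in the protocol bear on how study drug is stopped.

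- **Section 7.10 (withdrawal criteria)**, on participants withdrawn because of side effects: "Participants withdrawn from treatment for other clinical reasons (i.e. side effects) will not be weaned, but advised to stop study treatment with immediate effect". Its reason is: "Weaning of beta-blockers is advised when administered for cardiovascular indications, this is not the case in this trial". The same section sends participants who withdraw consent for treatment to the weaning schedule in 8.7.2.
- **Appendix 1 (risk)**, on participants with intolerable side effects: "For participants with intolerable side effects, wherever possible the dose of bisoprolol will be weaned down to zero wherever possible"; then, as the fallback, "if not the study drug will be stopped immediately". It calls the fallback acceptable because these people were not started on bisoprolol for cardiac disease.
- **Section 8.7.1 (general considerations)**: "Treatment should not be abruptly stopped (unless clinically indicated), but weaned off by one tablet a day per week to zero".
- **Section 8.7.2 (dose reduction at end of follow-up)** weans participants after the 12-month period "in order to avoid possible rebound myocardial ischemia". It adds: "A similar regime will be recommended for participants who wish to discontinue medication during the study". The drug and dosing part of section 2 gives the same ischaemia reason for weaning at the end of treatment.
- **Section 8.8**, where a beta-blocker or a significantly interacting drug becomes necessary: "no weaning will be required because of clinical necessity (although weaning can be carried out at the discretion of the treating clinician").

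**The concern.** Stopping because of side effects is foreseeable in this trial: unacceptable adverse effects are a listed reason for withdrawal in 7.10. For that event, the section sites would consult on withdrawal and the appendix that sets out how risk is controlled point in opposite directions. Two sites could treat the same situation differently and each cite the protocol. The risk control described in Appendix 1 would then not be what sites following 7.10 actually do.

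The protocol itself names a cardiac hazard of stopping. MACE and cardiac mortality are secondary outcomes (3.4), and treatment effects with and without clinically diagnosed heart disease are a secondary objective (3.2). Section 6.2 excludes heart failure, and myocardial infarction or acute coronary syndrome within the last year, but not all other diagnosed heart disease. The population in whom the named hazard could matter is narrowed, not removed.

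**Working it through.** This is a comparison of texts; the only arithmetic concerns how many participants could be affected.

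**1. Same people, opposite defaults.** Section 7.10 covers withdrawal for side effects and Appendix 1 covers intolerable side effects, so a participant taken off drug because side effects cannot be tolerated falls under both.

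| | Default | Exception stated |
|---|---|---|
| 7.10 | Stop at once, no weaning | None |
| Appendix 1 | Wean to zero | Immediate stop if weaning is not possible |

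Where weaning is not possible, both lead to an immediate stop. Where it is possible, they cannot both be followed.

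**2. Where the difference bites.** In the 8.7.2 table, a participant on one tablet a day stops outright, so the two instructions coincide. On two, three or four tablets the schedule takes one, two or three weeks to reach zero, and they diverge.

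**3. Section 8.7.1.** Its rule against abrupt stopping carries an exception for clinical indication, and 7.10 classes side effects among clinical reasons. The two can be read together. What 8.7.1 lacks is any statement of whether side effects count as such an indication.

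**4. Section 8.7.2 on who is weaned.** It recommends weaning for people who wish to discontinue. Section 7.10 sends those who withdraw consent for treatment to that same schedule. The two agree on that group.

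**5. Rationale.** Section 7.10 says weaning is advised for cardiovascular indications and that this trial is not such a case. Section 2 and 8.7.2 wean participants of this same trial because of possible rebound myocardial ischaemia. If the 7.10 reason holds for everyone, the stated purpose of the end-of-treatment wean falls away. If the 8.7.2 reason holds, the 7.10 reason does not by itself justify omitting a wean. Appendix 1 shares the 7.10 reasoning, but uses it only to accept the fallback.

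**6. Numbers.** Inputs from section 10.1: 787 randomised per arm and 15% expected to withdraw from study treatment.

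- 0.15 × 787 = 118.05, about 118 per arm.
- Check against the plan's own figures: 787 − 669 = 118.

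This counts every stop in the planning allowance, including consent withdrawals (weaned under 7.10), stops under 8.8, and participants on one tablet. The protocol does not state the share due to side effects, so the number affected lies somewhere between 0 and about 118 per arm on the plan's own assumption.

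**The case against.** The strongest reply is that the protocol broadly separates elective stops, which are weaned, from clinically driven ones, which need not be. Section 7.10 fits that pattern, as do the exception in 8.7.1 and the discretion in 8.8. On this view Appendix 1 is a stray default in a risk appendix, and it gives essentially the same reason as 7.10 for accepting an abrupt stop. That is a fair reading of the overall intent and limits the point largely to one section against one appendix. It does not remove it: Appendix 1 is current text, addresses the same participants and states the opposite default.

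Three stronger readings are tempting but not supported:

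- A reader might infer that 8.7.1 flatly contradicts 7.10. Its exception for clinical indication prevents that.
- A reader might infer that everyone except those stopping for side effects is weaned. Section 8.8 requires no weaning when a beta-blocker or significantly interacting drug is needed, and one-tablet participants simply stop under 8.7.2.
- A reader might infer that mixed stopping practice makes the MACE comparison uninterpretable. Allocation is blinded (7.4) and analysis is by intention to treat (10.3), so stopping practice is not chosen by arm. Any rebound events on bisoprolol would be part of the effect of being assigned to it.

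The documents also already provide some capture: SAEs are recorded until 28 days after ceasing study drug for those who stop early (9.2), and adverse effects during weaning go in the CRF (8.7.2). The protocol does not, however, state that the manner of an early stop is recorded.

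**Conclusion.** The contradiction between 7.10 and Appendix 1 is direct and is wrong as written. It rests on the wording of those two places alone. The conflict of rationale between 7.10 and section 2 with 8.7.2 is real but narrower: a tension in reasons, not a second pair of opposed instructions. Section 8.7.1 needs alignment rather than correction.

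The consequence is inconsistent handling of a foreseeable safety event, and difficulty in describing events after cessation if the manner of stopping is not recorded. No bias in the primary outcome or in the randomised MACE comparison is shown. At most about 118 participants per arm fall within the planning allowance for stopping drug, and the relevant fraction cannot be derived from the protocol. Nothing here implies that either stopping rule is the right one.

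**What to change.** - The sponsor and investigators should reconcile 7.10 and Appendix 1 into a single rule for participants stopping because of side effects. The choice of rule is theirs.
- Align 8.7.1 with that rule by stating whether side effects fall under its exception.
- Make the reasons in 7.10, section 2, 8.7.2 and Appendix 1 consistent with the rule and with each other.
- Record on the CRF, for each early stop, whether it was abrupt or weaned.

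A table of MACE by manner of stopping is optional. It would compare groups formed by clinical circumstance rather than randomisation, so it would be descriptive only.

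The cost is a protocol wording amendment, with the usual approvals, and one CRF item. Sample size and the primary analysis are unchanged.
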